### Safety evaluation

Treatment-associated adverse events (AEs) comprise dizziness, hematoma, broken needles, and infection. Researchers will document AEs in the CRF, noting dates, severity, relevance, and resolution. Proficient acupuncturists, well-versed in acupoint localization, precise manipulation, and aseptic procedures, along with the use of high-quality, disposable sterile needles, can effectively mitigate AEs. Patients’ preparation, ensuring they are neither hungry nor fatigued, further contributes to AE avoidance. In the occurrence of any observed AEs, acupuncturists will promptly evaluate their severity and undertake appropriate measures. These may encompass discontinuation of treatment, provision of rest post-dizziness, application of gentle pressure to mitigate bleeding and hematoma formation, or referral of the patient to a surgeon or physician for instances involving needle breakage or infection. Serious adverse events will be reported promptly to the safety committee and actively managed. Meanwhile, details of the termination of treatment will be recorded, including the final time and outcome, to aid in the statistical analysis of AEs.

### Sample size calculation

Sample size calculation utilized the ‘Test For Two Proportions (Test Version)’ module of PASS software (version 15.0.5, NCSS, LLC) with a two-tailed α of 0.05, power of 80%, and a 1:1 ratio. Based on our preliminary pilot results, the treatment response rate at week 4 was 33.3% (5/15) in the treatment group and 6.7% (1/15) in the control group, with an effect size of 0.71. The sample size encompasses 32 participants allocated to each group. Assuming a 20% dropout rate, the required sample size is 40 participants per group, totaling 80 participants.

### Statistical methods

Statistical analysis will employ SAS software for the full analysis set, per-protocol set, and safety set. Missing values will be handled using the last observation carryover method. Continuous variables will be presented as mean ± SD (normal distribution) or median (range) (non-normal distribution) and assessed with the t-test or Mann–Whitney U test. Categorical variables will be presented as frequencies or percentages and analyzed using chi-square or Fisher’s exact tests. CIs will be set at 95% with a significance level of 5% (*p* < 0.05). To avoid multiplicity, we will use a Bonferroni adjustment for multiple comparisons of fMRI among the treatment group, control group, and healthy subjects. With three groups (k = 3), the adjusted test level (α’) was set at 0.0167 (α/3 = 0.05/3). Pearson’s correlation will examine the association between changes in brain activity and clinical outcome improvement within each group. The success of blinding will be assessed using the Bang’s Index. In addition, to mitigate the influence of age and other confounding factors, we will employ covariance analysis on the continuous data.

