### Outcomes

The primary outcome measure is the treatment response rate, defined as the percentage of individuals whose total ISI score is decreased by ≥8 points from baseline at the end of treatment (week 4) (13).

ISI is a subjective and validated measure assessing various aspects of sleep, including sleep onset, maintenance, early awakening, dissatisfaction, interference with daytime functioning, life quality, and mental distress. The seven-item questionnaire uses a 0–4 scale, yielding a total score range of 0–28. Scores correspond to absence (0–7), mild (8–14), moderate (15–21), or severe (22–28) insomnia. The ISI is a concise, reliable tool commonly employed in general practice, sensitive to treatment response (14).

The secondary outcomes include the following eight items:

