Outcomes will be measured during four different time points: week 0 (the baseline), week 1 (the intervention period), week 4 (the post-treatment period), and week 8 (the follow-up period). At week 0, ISI scores, actigraphy, GAD-7, PHQ-9, and QLQ-C30 will be collected. At week 4, the primary and all secondary outcomes will be tested. At week 1, actigraphy will be measured to observe the short-term effect of treatment. At week 8, the primary and a few secondary outcomes (i.e., the change of ISI scores, the treatment remission rate, and the weekly usage of remedial drugs) will be recorded. Additionally, at week 0 and week 4, neuroimaging data will be acquired to test the neural effects of the treatments for CRI patients, while the healthy subjects only need to be scanned once at week 0 (the baseline). Moreover, weekly usage of remedial drugs will be measured from week 1 to week 8.

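### Last observation carried forward is the only missing-data rule, and with so few visits it copies baseline into week 4 and end-of-treatment ISI into week 8; the resulting bias has no predictable direction

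*Protocol article*

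**What the plan says.** The Statistical methods section of the protocol article deals with missing data in one sentence: "Missing values will be handled using the last observation carryover method". It is not limited to any outcome or visit, and no second method or sensitivity analysis is named.

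The visit schedule is in Table 1 and the Outcomes section:

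- Baseline: "At week 0, ISI scores, actigraphy, GAD-7, PHQ-9, and QLQ-C30 will be collected". Patients are also scanned at week 0.
- Week 1: "At week 1, actigraphy will be measured to observe the short-term effect of treatment". No questionnaire is scheduled.
- Week 4: "At week 4, the primary and all secondary outcomes will be tested".
- Week 8: of the questionnaires, only the ISI outcomes (response, remission, change).

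The primary endpoint is a fall in ISI of at least 8 points from baseline at week 4. Treatment ends at week 4. Sample size calculation expects losses: "Assuming a 20% dropout rate, the required sample size is 40 participants per group", which is 8 of 40 in each arm.

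**The concern.** Carrying a value forward is only as good as the last value available, and here that value comes from a different phase of the trial. For ISI, GAD-7, PHQ-9 and QLQ-C30 the only value before week 4 is the pre-treatment one, so every missing week-4 change is set to exactly zero. For ISI at week 8 it is the end-of-treatment score, so a responder lost after week 4 counts as still responding four weeks after the last session. For week-4 actigraphy it is a week-1 reading meant to show the short-term effect.

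Read literally for fMRI, the rule also copies a baseline scan into week 4 and feeds a zero brain change into the planned within-group correlations with clinical improvement. In every case a single imputed value is treated as observed, so its uncertainty is ignored.

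At stake are the size of the primary effect, the continuous comparisons, the only follow-up evidence on durability, and the correlations meant to inform mechanism.

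**Working it through.** **Inputs from the article (Sample size calculation).** Week-4 response p1 = 5/15 = 33.3% and p2 = 1/15 = 6.7%; two-sided α 0.05; power 80%; 32 per group before dropout; 20% dropout; 40 per group.

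**Reproducing the stated size.** With unpooled variance, n = (1.960 + 0.842)² × [p1(1−p1) + p2(1−p2)] / (p1−p2)² = 7.849 × 0.2844 / 0.0711 = 31.4, so 32. Then 32/0.8 = 40. Both stated figures reproduce.

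**Primary endpoint, week 4.** A dropout before week 4 gets change 0 and is a non-responder, so the expected rate is p × (1 − d). Assumption: dropouts would have responded like completers. Treatment/control dropout gives:

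- 20%/20%: 26.7% vs 5.3%, difference 21.3 points instead of 26.7
- 10%/10%: 24.0 points; 30%/30%: 18.7 points
- 10%/30%: 30.0% vs 4.7%, 25.3 points
- 30%/10%: 23.3% vs 6.0%, 17.3 points

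The difference exceeds the true one only if p2 × d2 > p1 × d1. At the planned rates this means control dropout more than five times treatment dropout.

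Power at 40 per group with 20%/20% dropout: standard error = √[(0.1956 + 0.0505)/40] = 0.0784; 0.2133/0.0784 − 1.960 = 0.76, giving 77.6%. Exact enumeration of the chi-square test gives 79.2%. With 32 completers per group the same two methods give 80.7% and 80.4%. The loss is small. It arises because the inflation from 32 to 40 assumes that dropouts leave the analysis, whereas the rule keeps them in as failures. By the formula that gave 32, about 43 per group would be needed.

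Type I error (exact chi-square, 40 per group):

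- Equal 20% dropout: 4.6% to 5.3% for common true rates of 6.7%, 20% and 33.3%.
- Dropout 10% vs 30%: false difference p × 0.20. At 33.3% this is 6.7 points and type I error 10.2%; at 20%, 4.0 points and 8.0%; at 6.7%, 1.3 points and 5.4%. The sign follows the arm with less dropout.

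**Continuous outcomes, week 4.** Assume an equal true mean improvement of 6 ISI points. Dropout of 10% vs 25% gives 6 × 0.90 − 6 × 0.75 = 0.9 points of spurious difference; reversing the arms gives −0.9. Equal 20% dropout gives 4.8 − 4.8 = 0.

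**Week-8 response.** Assume true week-8 rates of 20% vs 6.7% (difference 13.3 points), week-4 rates as planned, and 20% dropout in both arms:

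- All lost after week 4: 0.8 × 20% + 0.2 × 33.3% = 22.7% vs 6.7%; difference 16.0, overstated.
- Half lost before week 4 (baseline carried to week 8), half after: 0.8 × 20% + 0.1 × 33.3% + 0.1 × 0 = 19.3% vs 0.9 × 6.7% = 6.0%; difference 13.3, no bias.
- All lost before week 4: 0.8 × 20% = 16.0% vs 0.8 × 6.7% = 5.3%; difference 10.7, understated.

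**fMRI correlation, if scans are carried forward.** With a fraction d of (0,0) points, completer correlation r and mean changes mx, my in SD units: r* = [(1−d)r + d(1−d)mx·my] / √{[(1−d) + d(1−d)mx²][(1−d) + d(1−d)my²]}. For d = 0.2 and mx = my = 1:

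- r = 0: 0.16/0.96 = 0.17, away from zero
- r = −0.3: (−0.24 + 0.16)/0.96 = −0.08, toward zero

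A (0,0) point needs both the scan and ISI to be missing at week 4. A missed scan alone gives zero brain change against an observed ISI change.

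**The case against.** The strongest objection concerns the primary endpoint. With only baseline before week 4, the rule is non-responder imputation under another name. Declaring it openly, as proposed below, leaves the data, the test and the p-value unchanged, and the small power loss remains. A reader might infer that the primary test is invalid. The article does not support that: it gives a single dropout figure, and with equal dropout type I error stays near 5% and the effect is shrunk, which is conservative for a superiority claim. This objection stands and limits the severity.

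A reader might also infer that the rule systematically favours acupuncture at week 8, or inflates the fMRI correlations. Neither follows. The same 20% dropout overstates, leaves unchanged or understates the week-8 difference according to when patients leave, and the correlation can move either way. Differential dropout and relapse rates are assumptions; the article states neither. It also nowhere says explicitly that a scan will be copied; that is the literal reach of a general sentence.

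Finally, imputation detail often belongs in an analysis plan that is not shown. That would answer a silent protocol, but this one names a rule for all missing values. The per-protocol set it lists is not a missing-data method. The planned covariance analysis does not help either, because the imputed zeros enter it as observed outcomes.

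**Conclusion.** The point holds as a weakness in the stated rule, at should-fix level. It is certain from the schedule that the rule carries baseline into week 4 for the questionnaires, end-of-treatment ISI into week 8, and week-1 actigraphy into week 4, in a trial planned for 20% dropout.

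For the primary endpoint the effect is undeclared non-responder imputation. The expected difference is 21.3 rather than 26.7 points at equal 20% dropout, if dropouts would have responded like completers. Type I error is then near 5%; it rises to about 10% only under an assumed 10% vs 30% imbalance with a common response rate of 33.3%.

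For the continuous, week-8 and fMRI outcomes, the size and direction of the bias cannot be determined from the article. The rule therefore cannot be defended as uniformly conservative, nor condemned as uniformly inflating.

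**What to change.** Replace the single sentence with rules by outcome:

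- **Primary endpoint:** state that a missing week-4 ISI counts as non-response, with multiple imputation as a sensitivity analysis.
- **ISI change (weeks 4 and 8) and actigraphy (weeks 1 and 4):** a baseline-adjusted mixed model for repeated measures, or multiple imputation by arm.
- **GAD-7, PHQ-9 and QLQ-C30 (week 4):** baseline-adjusted ANCOVA, with multiple imputation if needed.
- **Week-8 response and remission:** derive from multiply imputed ISI, not from the carried week-4 value. Say openly that this differs from the week-4 rule, since a patient missing both visits is a fixed non-responder at week 4 but may be an imputed responder at week 8.
- **fMRI change and correlations:** only participants with both scans; no scan carried forward.

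The cost is about a paragraph of text, slightly more analysis work and somewhat wider confidence intervals. No new data are needed. The change does not recover the small power loss on the primary endpoint, which comes from counting dropouts as failures.

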Therefore, the purpose of this study is to examine the clinical efficacy and safety of acupuncture in treating CRI. Our investigation will comprehensively assess patients’ sleep through subjective and objective measures. Furthermore, due to the lack of functional imaging studies on CRI, this trial will incorporate functional magnetic resonance imaging (fMRI) to explore the potential neural mechanisms underlying the effectiveness of acupuncture in treating CRI.

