## Discussion

Acupuncture has been utilized in the treatment of insomnia in China since ancient times. Previous single-group or pilot trials have demonstrated that acupuncture treatment, either alone or in combination with auricular acupressure, can be advantageous for improving sleep quality (10, 11) among cancer survivors. The efficiency of acupuncture surpasses fluoxetine or tamoxifen in improving insomnia symptoms and reducing cancer-related mental disorders (19, 20). Notably, the comparisons with positive drugs should be interpreted with caution as these agents are not specifically targeted for sleep-related conditions. Moreover, studies have revealed that acupuncture treatment can improve sleep onset latency, total sleep time, and sleep efficiency; however, compared to sham control, acupuncture does not exhibit a significant difference in reducing ISI (21). Therefore, the confirmation of acupuncture’s superiority over sham control remains unresolved. In summary, the paucity of studies exploring curative effects necessitates a blinded randomized clinical trial to validate existing findings. The mechanisms of acupuncture in treating CRI are still unknown.

Abnormal activity has been observed in multiple brain regions, including the prefrontal lobe, temporal lobe, parietal lobule, anterior cingulate, supramarginal gyrus, and precuneus among victims of insomnia. Remarkably, acupuncture has demonstrated a significant improvement in symptoms of insomnia and the ability to modulate brain activity in these regions (22–24). Consequently, we propose that acupuncture may also ameliorate CRI by influencing the activity of correlated brain regions. To investigate this, we have designed a randomized controlled trial to assess the effects of acupuncture on CRI, with a specific focus on its impact on the hyperarousal state of the brain, as measured by fMRI methods.

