## Conclusion

This research endeavors to assess the effectiveness of acupuncture for patients with CRI when contrasted with sham acupuncture. Additionally, our study seeks to delve into the underlying neuropathological mechanisms of CRI while employing fMRI to investigate the distinct neural response characteristics elicited by acupuncture treatment.

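### Brain change is linked to symptom improvement only by separate correlations within each arm, which cannot show that the link differs from sham or that brain change carries acupuncture's effect

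*Protocol article*

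**What the plan says.** Under Statistical methods, the Protocol article uses Pearson's correlation to "examine the association between changes in brain activity and clinical outcome improvement within each group". Outcomes has the healthy subjects scanned once, at baseline. Change data therefore exist only in the two randomized arms, and the analysis amounts to two parallel correlations for each brain measure.

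The same section plans a "Bonferroni adjustment for multiple comparisons of fMRI among the treatment group, control group, and healthy subjects", with an adjusted level of 0.0167. It also says that "to mitigate the influence of age and other confounding factors, we will employ covariance analysis on the continuous data". It names no comparison of the two correlations, no model spanning both arms and no mediation analysis.

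The mechanistic aims are worded in three places:
- Background and objective: to "explore the potential neural mechanisms underlying the effectiveness of acupuncture in treating CRI".
- Discussion: "we propose that acupuncture may also ameliorate CRI by influencing the activity of correlated brain regions", with the trial presented as designed to investigate this.
- Conclusion: to "investigate the distinct neural response characteristics elicited by acupuncture treatment".

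**The concern.** The Discussion's proposal is causal: acupuncture changes brain activity, and that change improves insomnia. The sham arm is what separates this from changes that accompany any improvement. The correlation analysis is the only planned step that ties brain to symptoms, and it does not use sham as a comparator.

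The natural way to read two within-arm results is to contrast them: significant under acupuncture, not significant under sham, hence something particular to acupuncture. That inference is invalid, because a difference in significance is not a significant difference. With about 32 to 40 patients per arm and moderate correlations, discordant p-values are common even when the two arms share the same correlation. At stake is an unsupported mechanistic claim from a secondary outcome.

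**Working it through.** **Inputs from the plan.** Sample size calculation gives 32 per arm, raised to 40 for 20% dropout, two-sided 5%, 80% power, and response rates of 5/15 and 1/15. These figures serve the primary outcome; no power is given for the correlations.

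**Reproducing the plan's figure.** Cohen's h = 2·asin√(1/3) − 2·asin√(1/15) = 0.709, matching the stated effect size of 0.71. Then n = 2·[(1.960 + 0.842)/0.709]² = 31.3, so 32, and 32/0.80 = 40. I use 32 and 40 as the numbers per arm.

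**Assumptions.** The documents give no correlations, so r is assumed. I take every counted patient to have both scans, the arms to be independent, and each correlation to be tested at two-sided 5%. The 0.0167 level is tied to the group comparisons and is not stated to cover the correlations.

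**Step 1: power within one arm.** On the Fisher z scale, p ≈ Φ(√(n − 3)·atanh r − 1.96). For n = 32 and r = 0.4: √29 × 0.424 = 2.28, and Φ(0.32) = 0.626. Simulation of the Pearson test gives 0.638.

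**Step 2: significant under acupuncture only.** With the same true r in both arms, this probability is p(1 − p).

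| n per arm | r | p | p(1 − p) |
|---|---|---|---|
| 32 | 0.2 | 0.194 (Fisher) | 16% |
| 32 | 0.3 | 0.393 (simulated) | 24% |
| 32 | 0.4 | 0.638 (simulated) | 23% |
| 32 | 0.5 | 0.841 (Fisher) | 13% |
| 40 | 0.2 | 0.234 (Fisher) | 18% |
| 40 | 0.3 | 0.476 (simulated) | 25% |
| 40 | 0.4 | 0.746 (simulated) | 19% |
| 40 | 0.5 | 0.916 (Fisher) | 8% |

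A direct two-sided 5% test of the difference errs in the acupuncture direction in 2.5%. The rates are per brain measure, and Outcomes lists ALFF, ReHo and seed-based FC.

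**Step 3: an example.** With n = 32, an observed r = 0.40 has p = 0.023 and an observed r = 0.30 has p = 0.095. The difference is (0.424 − 0.310)/√(2/29) = 0.43 standard errors, p = 0.66.

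**Step 4: what a joint analysis can deliver.** The standard error of Fisher z within an arm is 1/√29 = 0.186 (n = 32) or 1/√37 = 0.164 (n = 40). Pooled over both arms with a common correlation it is 1/√58 = 0.131 or 1/√74 = 0.116. The difference between arms is much less precise: 80% power needs a Fisher z difference of 2.80·√(2/29) = 0.74 or 2.80·√(2/37) = 0.65. That means r = 0.63 or 0.57 under acupuncture against 0 under sham. For r = 0.5 against 0.2, power is only 26% or 32%.

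**The case against.** **Aim.** A reader might infer that the trial states an aim of showing a brain-symptom link specific to acupuncture. No section says so. The Background speaks of exploring mechanisms, and the Conclusion speaks of neural response, which is a different quantity from the link to symptoms. This stands.

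**Comparison with sham.** A reader might also infer that the fMRI analysis never uses the sham arm. It does: the Bonferroni-adjusted group comparisons address whether the brain response differs from sham, and so serve the Conclusion's aim. They do not address how that response relates to symptoms.

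**Shared link.** It is tempting to say that an equal brain-symptom link in both arms would point to improvement in general and against an acupuncture mechanism. That does not follow. If acupuncture shifts brain activity more than sham and the slope is equal, the Discussion's proposal is supported while the interaction is zero. An interaction test alone would therefore be the wrong remedy.

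**Size.** Counting trials in which exactly one arm is significant gives 38-50% for r = 0.3 to 0.4. Half of these are sham-only results, which suggest nothing particular to acupuncture, so that count overstates the harm.

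**Status.** fMRI is one of eight secondary outcomes, the article contains no rule that discordant p-values will be read as specificity, and model detail may sit in a fuller document. This lowers the stakes but does not remove the point. The article does not merely leave the method open; it fixes a within-arm method that cannot serve the mechanistic proposal.

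**Conclusion.** The point holds as a limit on what the stated analysis can support. Separate within-arm correlations can describe each arm. They cannot show that the brain-symptom link differs from sham, and they cannot show that brain change carries acupuncture's effect. If the true correlation is equal at 0.3 to 0.4, an acupuncture-only pattern appears in about 23-24% of trials per measure with 32 per arm and about 19-25% with 40 per arm, against about 2.5% for a direct test. At r = 0.2 or 0.5 the rate is lower, 8-18%. These figures rest on assumed correlations, complete paired scans and 5% testing of each correlation.

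The documents do not support the stronger reading that the plan is unable to show any acupuncture-specific brain response, because that comparison with sham is planned. The change is worth making because a better analysis uses data already collected.

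**What to change.** For each brain measure chosen in advance, fit one exploratory model across the two randomized arms, with ISI change regressed on arm, brain change and baseline ISI.

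- Report the common slope with a 95% CI. It uses both arms and is more precise than either within-arm correlation.
- Add the arm-by-brain-change interaction and report it with a 95% CI. Any statement that the link differs between arms should rest on this term.
- Base any statement that acupuncture works through brain change on the between-arm difference in brain change together with the joint-model slope, as a mediation estimate with a CI. Do not base it on the interaction.
- Keep the within-arm correlations as description only.

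The cost is analysis wording and a few models per measure, with no new data. The interaction will be imprecise at this sample size, as shown above. The mediation estimate assumes no unmeasured confounding between brain change and symptom change, which randomization does not guarantee. Both should be labelled exploratory, and fewer mechanistic claims will be possible.

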### Criteria for inclusion

For CRI patients, the inclusion criteria are as follows:

Meet the diagnosis of stage I to III breast cancer and also meet the DSM-IV diagnostic criteria for insomnia, the symptoms of which occurred after breast cancer diagnosis and lasted for at least 1 month.Aged 18 to 75 years, female.Eastern cooperative oncology group performance status score ≤ 2.Sleep severity index (ISI) score ≥ 8.Survival prediction ≥6 months.No prior acupuncture treatment.Right-handed.No MRI contraindications such as MR-incompatible metal implants or claustrophobia.Consent to participate and provide written informed consent.

For healthy subjects, the inclusion criteria are as follows:

Age-, hand dominance-, and educational level matched to the selected CRI patients.Self-reported good sleep quality with an ISI score of <8.Absence of previous functional or organic disease or history of head trauma.No MRI contraindications for the CRI patients.Consent to participate and provide written informed consent.

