The change in ISI scores.The treatment remission rate: the percentage of people with ISI < 8.Actigraphy sleep assessment: It is a watch-shaped device to objectively record sleep patterns. It includes measurements of total sleep duration (TST), sleep–wake duration (WASO), and sleep efficiency (SE). Consequently, actigraphy serves as an effective tool for evaluating sleep quality in cancer patients (15).Generalized Anxiety Disorder Scale (GAD-7): It is a concise anxiety self-assessment instrument consisting of seven items scored on a 0–3 scale, yielding a total score range of 0–21. Scores of 5–9 indicate mild anxiety, 10–14 suggest moderate anxiety, and 15–21 represent severe anxiety (16).Patient Health Questionnaire-9 (PHQ-9): This nine-item validated depression self-assessment tool scored on a 0–3 scale, with a total score range of 0–27. Interpretation of scores categorizes depression as mild (5–9), moderate (10–14), severe (15–19), or very severe (20–27) (17).Quality of Life Core Scale (QLQ-C30): This 30-item questionnaire evaluates the QoL among cancer survivors. It comprises functional scales (physical, role, cognitive, emotional, and social functioning), a global QoL scale, symptom scales (fatigue, nausea and vomiting, and pain), and single items (appetite loss, diarrhea, dyspnea, constipation, insomnia, and financial impact) (18).The weekly usage of remedial drugs: The percentage of participants who used hypnotic medications.fMRI: The fMRI data will be pre-processed and analyzed using SPM8 software platform (SPM8, Wellcome Department of Imaging Neuroscience, London, United Kingdom) with MATLAB 2016b (MathWorks, Inc., Natick, MA, United States). Images will be pre-processed, including artifact correction (AFNI and RETRO-ICOR), head motion correction (FSL and MCFLIRT), and brain extraction (FSL and BET). Cortical surface reconstruction with boundary-based registration (FreeSurfer and bbregister) enhances structural–functional co-registration. After spatial smoothing and high-pass temporal filtering, various analytical methods (ALFF, ReHo, and seed-based FC) will assess neural response.

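### Continuous outcomes have two unranked analyses, one unadjusted and one by covariance analysis, and the outcome's own baseline value is not named as the covariate: an avoidable loss of precision

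*Protocol article*

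**What the plan says.** All of the analysis text is in one paragraph of the protocol article, under Statistical methods.

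- Continuous variables are "assessed with the t-test or Mann–Whitney U test", depending on whether they look normally distributed. Neither test uses a covariate.
- Categorical variables are "analyzed using chi-square or Fisher’s exact tests". The primary outcome is binary (a fall of at least 8 ISI points by week 4), so this is the only between-group test stated for it.
- The paragraph ends with an additional step: "to mitigate the influence of age and other confounding factors, we will employ covariance analysis on the continuous data". Age is the only covariate named, and the step is confined to continuous data.

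The Outcomes section shows which baseline values will be available: "At week 0, ISI scores, actigraphy, GAD-7, PHQ-9, and QLQ-C30 will be collected". Among the secondary outcomes is "The change in ISI scores", where baseline enters by subtraction.

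**The concern.** Each continuous outcome has two between-group analyses, and the first has two forms that depend on a normality check. Nothing states which result is the headline. The analyses can disagree, so the choice could be made after the results are seen.

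The reason given for adjustment also points away from the useful covariate. In a 1:1 randomised comparison, baseline differences between the arms are due to chance, so there is no systematic confounding to remove. Adjustment is worthwhile because it gains precision and corrects for chance imbalance. For both purposes the natural covariate is the baseline value of the same measure, which will be in the database for every scale and for actigraphy. With about 32 evaluable patients per arm, that precision is worth having.

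**Working it through.** **Inputs from the article (Sample size calculation):** two-sided α 0.05; power 80%; 1:1 allocation; response 5/15 against 1/15; effect size 0.71; 32 evaluable per arm; 20% dropout; 40 per arm.

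**Assumed input:** baseline/follow-up correlation r of 0.3, 0.5 and 0.7. The article gives no correlation.

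**1. The plan's own figure.** h = 2·asin√(1/3) − 2·asin√(1/15) = 0.709, which matches the stated 0.71. n = 2·((1.960 + 0.842)/0.709)² = 31.3, rounded up to 32 per arm, and 32/0.80 = 40. The sample size reproduces, so this point implies no sample-size error.

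**2. Variance of the between-arm comparison.** Take equal standard deviations σ at baseline and follow-up, a common slope in both arms, and ignore the one degree of freedom spent on the covariate.

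- Unadjusted change score: proportional to 2σ²(1 − r)
- ANCOVA on the baseline value: proportional to σ²(1 − r²)
- Ratio: (1 − r²)/[2(1 − r)] = (1 + r)/2

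**3. Power.** At 32 per arm, 80% power needs a standardised difference of (1.960 + 0.842)·√(2/32) = 0.70. For an effect of that size on the change score, ANCOVA power is Φ(2.802/√ratio − 1.960).

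| Assumed r | Variance ratio | Power, change-score t-test | Power, ANCOVA | n per arm for the same precision as 32 |
|---|---|---|---|---|
| 0.3 | 0.65 | 80% | Φ(1.515) ≈ 94% | 20.8 |
| 0.5 | 0.75 | 80% | Φ(1.275) ≈ 90% | 24.0 |
| 0.7 | 0.85 | 80% | Φ(1.079) ≈ 86% | 27.2 |

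**4. If the week-4 score is compared instead of the change.** The article specifies change for ISI but not for the other scales. The ratio against an unadjusted final score is 1 − r² = 0.91, 0.75 and 0.51, and an 80% power becomes about 84%, 90% and 97.5%. ANCOVA is more precise than either unadjusted form throughout this range. The Mann–Whitney alternative was not evaluated.

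**5. The binary primary.** Expected responders: 32 × 1/3 + 32 × 1/15 = 10.7 + 2.1 = 12.8, about 13 among 64. Two simulations at 32 per arm bear on adjustment for baseline ISI.

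- With simulated ISI data, adjusted logistic regression had 78–82% power against 80–84% for chi-square, so no gain.
- With an assumed log-odds per baseline SD of 0, 0.5, 1.0 and 1.5, a linear adjusted analysis had about 80, 82, 84 and 87%, against 80, 81, 81 and 80% unadjusted.

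A clear gain appears only at the strongest assumed association.

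**The case against.** The strongest defence is that this is a condensed article. It does plan a covariance analysis of continuous data, its reference to further factors is open-ended, and covariate lists usually sit in an analysis plan that is not shown. This stands in part. A missing covariate list alone would be no finding, and a reader who inferred that baseline scores go unused would be wrong: nothing excludes them as covariates, and baseline ISI already enters by subtraction in the change score and the responder definition. What remains is in the text itself: two analyses with no stated order, and a rationale of confounding. The covariance step is introduced as an addition, which suggests that the unadjusted test leads, but the article does not say so.

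Three stronger readings are tempting and not supported.

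- *The change-score comparison is biased by regression to the mean.* Under randomisation the expected regression is the same in both arms and cancels. Only chance imbalance and lost precision remain.
- *Baseline adjustment explains the large power advantage of a continuous ISI analysis over the responder test.* Under a normal model, response rates of 33.3% and 6.7% imply a difference of 1.07 SD in the change score. An unadjusted t-test at 32 per arm already has about 99% power for that. The advantage comes from not dichotomising.
- *The unadjusted primary test is a flaw.* It is valid and matches the two-proportion basis of the sample size. With about 13 responders, a simple test is a reasonable choice.

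**Conclusion.** The point holds as a no-cost improvement in efficiency and pre-specification for the continuous secondary outcomes. The planned tests are valid, and no bias or sample-size error is shown.

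Against a change-score comparison, ANCOVA on the outcome's own baseline value cuts variance by 35%, 25% and 15% at r = 0.3, 0.5 and 0.7. These sizes rest on assumed correlations, equal variances at the two times and a linear relation with a common slope. They would be lost only if the unadjusted test is the main analysis or the covariance analysis omits the baseline value. The article leaves both open.

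For the primary, adjustment is optional. Entry requires "Sleep severity index (ISI) score ≥ 8" and response a fall of at least 8, so a patient who enters at 8 responds only by reaching 0. A chance imbalance in baseline severity could therefore affect the response rates, and guarding against that is the reason to adjust. Little or no power gain should be claimed for it.

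**What to change.** 1. Name ANCOVA, with the baseline value of the same outcome as covariate, as the single main analysis of each continuous outcome.
2. Keep the t-test or Mann–Whitney test as a sensitivity analysis only, so that a normality check no longer decides the headline result.
3. Give precision and chance baseline imbalance, not confounding, as the reason for adjustment. If age or another covariate is kept, name it in advance.
4. Optionally, add a supportive risk difference for the primary, adjusted for baseline ISI only (for example, a standardised estimate from logistic regression). With about 13 expected responders the model should hold no further covariates. The chi-square or Fisher test stays as the main analysis.

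The cost is a few sentences of analysis wording, settled before unblinding. All the baseline values are already scheduled for collection, and the sample size does not change.
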